### Methods for additional analyses (e.g. subgroup analyses) {27d}

After the completion of data collection, the data will be reviewed for suitability of the following analyses: Post hoc comparisons may be conducted for detailed analysis through between group and within group measures in case prior statistical analysis indicates significant differences. The moderating effect of changes in inhibitory control and stimulus devaluation immediately post intervention on changes in overt aggression behaviours at 1-month and 3-months post-intervention may be analysed.

The moderating effect of changes in inhibitory control and aggressive behaviour immediately following the intervention and at 1-month post-intervention on changes in substance use frequency and gambling behaviour at 1-month and 3-months post-intervention may be analysed.

If a significant dropout rate occurs during the study, an analysis can be conducted to identify any patterns or trends in the characteristics of participants who dropped out. This analysis can help understand potential reasons for dropout in terms of demographic, clinical, or other factors associated with higher dropout rates.

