### Objectives {10}

The primary objective of this study will be to evaluate the efficacy of Inhibitory Control Training (ICT) in reducing overt aggressive behaviours among individuals with co-occurring substance use disorder and gambling behaviour. Additionally, the study aims to assess whether reductions in aggression and improvements in inhibitory control will be associated with subsequent changes in substance use patterns and gambling behaviour over follow-up periods.

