### Trial design {12}

The research study will utilize a two-group, parallel, superiority randomized controlled trial (RCT) design. The primary objective of the trial is to determine whether inhibitory control training produces a greater reduction in aggressive behaviour compared to sham training, thereby testing the superiority of the experimental intervention over the comparator. Although the trial is designed as a superiority study, some aspects of it may be exploratory in nature due to our interest in whether the intervention works and how it works. Eligible participants will be randomly allocated in a 1:1 ratio to either the experimental group or the control group. In the experimental group, participants will receive inhibitory control training, while those in the control group will receive a sham version of the training. Both groups will also be receiving treatment as usual (TAU), as decided by the clinical team. Evaluation will occur at four time points: Pre-intervention (baselines), post-intervention at 1-Day post ICT, 1-month post ICT (± 4 Days), and 3-months post ICT (± 7 Days). The trial is designed to evaluate the superiority of Inhibitory Control Training over sham training in reducing aggressive behaviours.

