#### Study instruments for secondary outcomes

The Inhibitory Control Task will be based on a cue-based ‘Frequent Go/Rare No-Go Paradigms’ [31]. Participants will be directed to respond to pictures contained in circles by ‘pressing the space bar’ and to withdraw responses to pictures contained in squares. The go cue will be presented with 100% consistency with non-aggressive stimuli, and the no-go cue with aggressive stimuli. The task will have 20% no-go cues and 80% go cues, in accordance with the frequent go/rare no-go arrangement, as presented in Table 3. The task will have a single session with five blocks, bringing it up to 250 trials. The task will be administered prior to and following the ICT. The task, prior to and post intervention, will be preceded by 10 trials of practice sessions utilizing non-aggressive stimuli in squares and circles as no-go and go cues, respectively. The participants will be provided feedback on incorrect and correct responses during the practice trials. The practice sessions will not be recorded or scored [18, 20, 32]. Commission and omission errors will be recorded. Based on the results of a research study estimating the reliability of associative Go/No-Go Tasks, our task with 50 trials per block is indicated to have an acceptable reliability between 0.60 and 0.80 [33].

**Table 3 Tab3:** Details of one block of the inhibitory control task

Test	Aggressive Stimuli (AS)		Non-Aggressive Stimuli (NAS)		Duration of Presentation	Total Time
	Proportion	Number [T (/C)]	Proportion	Number [T (/C)]		
Pre-Test	20%	10 (2)	80%	40 (8)	1500 ms	15 Minutes
Post-Test	20%	10 (2)	80%	40 (8)	1500 ms	15 Minutes

*T (/C)* Total Pictures (Pictures Per Category)

The Stimulus Evaluation Task is an explicit, self-paced task which will instruct the participants to evaluate the aggressive pictures on an 11-pointer scale (0 to 10). The selection of pictures utilized during the training sessions and the main task will be determined by the patient’s rating on the Stimulus Evaluation Task. For the ICT, the highest-rated pictures will be used and for the sham training, the lowest-rated pictures will be employed. The 15 pictures not covered during the training will be included in the pre-test and post-test task to investigate the occurrence of generalization, defined as the transfer of inhibitory learning to untrained aggressive stimuli, which may indicate potential generalization of effects beyond the training context to real-world situations [18].

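### The additional analyses call post-randomisation changes 'moderators', although the mechanism question they serve is one of mediation, and one permitted pairing is concurrent

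*Protocol article*

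**What the plan says.** The additional analyses {27d} contain two mechanism analyses, both introduced as moderation.

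- The first is "The moderating effect of changes in inhibitory control and stimulus devaluation immediately post intervention on changes in overt aggression behaviours", with aggression taken at 1 and 3 months.
- The second concerns the moderating effect of changes in inhibitory control and aggression "immediately following the intervention and at 1-month post-intervention on changes in substance use frequency and gambling behaviour at 1-month and 3-months post-intervention".

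Both are optional: "After the completion of data collection, the data will be reviewed for suitability of the following analyses".

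Two statements elsewhere show what they are for. Trial design {12} says "some aspects of it may be exploratory in nature due to our interest in whether the intervention works and how it works". Objectives {10} asks whether reduced aggression and better inhibitory control "will be associated with subsequent changes in substance use patterns and gambling behaviour over follow-up periods". Expected outcomes, in the Discussion, goes further. It names inhibitory control and stimulus ratings as the place to look for the underlying mechanism, and it expects the changes to contribute to later reductions in substance use and gambling.

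On measurement, the section on secondary-outcome instruments says of the Inhibitory Control Task: "The task will be administered prior to and following the ICT". Table 3 has a pre-test row and a post-test row. Plans for assessment {25a} lists the same task among the measures taken at four time points.

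**The concern.** A moderator is a characteristic, normally fixed before randomisation, across whose levels the treatment effect differs. A mediator is something the treatment changes and through which it then acts. Changes in inhibitory control, stimulus ratings and aggression after training belong to the second kind: they follow randomisation, and the training exists to cause them.

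A moderation model asks whether the training works better in people whose inhibitory control happened to change more. That conditions on a variable the training has itself altered, so it has no clean reading as effect modification and estimates no indirect effect. A training that worked exactly as theorised could show no moderating effect at all, and the null result could be read as evidence against the mechanism.

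There is also a point about time order. The objective concerns later change, and the second analysis as worded allows predictor and outcome to be taken at the same visit.

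**Working it through.** **Which question, which model.** The protocol gives no figure here to reproduce, so the first check sets its sections side by side.

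- Trial design {12} and Expected outcomes ask how the training works, with inhibitory control and stimulus ratings as the route. That is group → early change → later outcome, which is mediation.
- Objectives {10} asks whether earlier change is associated with later change. A regression of later on earlier change answers this; no interaction is needed.
- {27d} names a moderating effect, which answers neither question directly.

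**Time order.** Taking every combination that {27d} allows:

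| Analysis | Change measured at | Outcome at | Order |
|---|---|---|---|
| First (aggression) | 1 day | 1 month | lagged |
| First (aggression) | 1 day | 3 months | lagged |
| Second (substance use, gambling) | 1 day | 1 month | lagged |
| Second | 1 day | 3 months | lagged |
| Second | 1 month | 1 month | concurrent |
| Second | 1 month | 3 months | lagged |

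Both pairings in the first analysis are ordered, as are three of the four in the second. The second sentence can also be read as successive pairs (1 day to 1 month, 1 month to 3 months), in which case none is concurrent.

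**What a moderation test would show if the mechanism were real.** The check simulates full mediation with no interaction:

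- M = a × group + e₁ and Y = b × M + e₂, with standard normal errors.
- Moderation test: the coefficient of group × M in Y ~ group + M + group × M, two-sided 5%.
- Mediation test: joint significance of a (M ~ group) and b (Y ~ group + M), each two-sided 5%.
- Numbers per arm: 26 is the stated requirement, and also what remains of 65 after the planned 60% attrition (65 × 0.40 = 26). About 35 remain after the 45% loss expected at 1 month (65 × 0.55 = 35.75). 65 is the number randomised.
- The values of a and b are assumptions, because the protocol gives none. There were 3,000 runs per setting.

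| Per arm | a, b | Interaction rejects | Joint test rejects |
|---|---|---|---|
| 26 | 0.5, 0.5 | 5.1% | 38.4% |
| 26 | 0.7, 0.5 | 5.2% | 64.4% |
| 26 | 1.0, 0.7 | 5.3% | 93.9% |
| 35 | 0.5, 0.5 | 5.0% | 51.7% |
| 35 | 0.7, 0.5 | 5.4% | 80.8% |
| 35 | 1.0, 0.7 | 4.2% | 98.8% |
| 65 | 0.5, 0.5 | 5.3% | 81.2% |
| 65 | 0.7, 0.5 | 5.1% | 96.6% |
| 65 | 1.0, 0.7 | 4.9% | 100% |

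The simulation error of a 5% rate is √(0.05 × 0.95 / 3,000) = 0.4 percentage points, so every interaction figure is compatible with 5%.

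Weaker paths lower the mediation figures. With b = 0.3 and a from 0.3 to 0.7, the joint test rejects in about 9% to 35% of trials at 26 per arm and about 17% to 57% at 36 per arm.

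**The case against.** **The interaction model is not in the protocol.** {27d} never writes a group-by-change term, and its wording could also describe a plain association between early and later change. The 5% follows by construction, since the data were generated without an interaction. With a = 0.7 and b = 0.5, a simple association of M with Y is detected in about 94% of trials at 26 per arm and 99% at 36. This stands, and it makes the consequence conditional: the pathway is missed if the analysis is run as moderation in the usual sense. It does not rescue the term, which names one kind of model while the stated question needs another.

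**Time order.** A reader might infer that the plan cannot address later change at all. The documents do not support that. The first analysis is fully lagged, only one of four pairings in the second is concurrent, and Objectives {10} asks only for association.

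**Task schedule.** A reader might infer that no 1-month inhibitory-control change will exist. The instrument section does not say the task is limited to two visits, {25a} lists it at four, and the schedule figure and the supplementary table of time points are not shown. What remains is an apparent inconsistency to reconcile.

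**Low stakes.** The analyses are optional, the interest in mechanism is flagged as exploratory, and the randomised contrast of 100% with 50% contingency bears on mechanism without them. This stands and limits the severity. However, these are the analyses the article offers for linking aggression and inhibitory control to substance use and gambling, and they name a specific method that does not fit.

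**Conclusion.** The point holds in a limited form. {27d} names the wrong analysis for the mechanism question, because the changes it calls moderators are candidate mediators. Run as a group-by-change interaction, the analysis gives no indirect effect and, for a linear pathway with no true interaction, rejects at about 5% whatever the path sizes. How much a mediation analysis would recover is uncertain: about 38% to 94% at 26 per arm over the main assumed range, and less below it. Those figures rest on assumed paths, so they illustrate the contrast and do not predict this trial's power.

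On time order the fault is narrow: one pairing, 1 month with 1 month, cannot support a claim about subsequent change. Nothing here touches the primary between-group comparison of OAS-M change.

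**What to change.** In {27d}:

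1. Replace the moderating effect with an exploratory mediation analysis: group → early change → later outcome, adjusted for the baseline values of mediator and outcome. Report the indirect effect with a bootstrap interval.
2. State the assumption of no unmeasured mediator-outcome confounding. Randomisation does not secure it, because the mediator is not randomised.
3. Use all the time-ordered pairings: 1 day to 1 month, 1 day to 3 months and, for substance use and gambling, 1 month to 3 months. Keeping only the last would discard valid lags, rest everything on the visit with the heaviest attrition, and leave no inhibitory-control path if the task is not given at 1 month.
4. Drop the 1-month/1-month pairing or label it cross-sectional.
5. Keep the word moderator for baseline variables.
6. Reconcile the instrument section and Table 3 with {25a} on when the Inhibitory Control Task is given, and use a 1-month inhibitory-control change only if it is given then.

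One caution when interpreting the results: the OAS-M covers the prior week, so the 1-day aggression score includes days before and during training and is a weak measure of early post-training change.

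The cost is a rewritten paragraph and one reconciled line on task timing. No new data are needed if the task is given as {25a} states. Enrolment is planned to run to December 2026, so the timing should be settled now: a visit without the task cannot be recovered later.

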### Interim analyses {28b}

No interim analyses are planned for this trial. Given the short duration of the intervention, the low-risk nature of the behavioural training, and the modest sample size, no formal stopping guidelines have been established. All analyses will be conducted after completion of data collection.

### Protocol and statistical analysis plan {5}

The full trial protocol, including the statistical analysis plan, is being submitted for publication and will be publicly accessible upon publication. The statistical analysis plan is integrated within the protocol document. The same data will also be available the Clinical Trials Registry of India (CTRI). Any substantive deviations from the pre-specified analysis plan will be clearly documented and justified in subsequent publications.

## Oversight and monitoring

### Composition of the coordinating centre and trial steering committee {3d}

This research study is being conducted as part of the doctoral thesis of the primary investigator. Oversight of the trial will be provided by a Doctoral Committee comprising seven members with expertise in psychiatry, clinical psychology, and/or biostatistics. This committee will be responsible for supervising the overall conduct of the trial, providing academic, methodological, and implementational guidance, and reviewing trial progress at scheduled meetings. No relevant decisions can be made with regards to the trial without consent from all 7 members of this committee. The protocol has also been formulated under the supervision of the doctoral committee.

### Composition of the data monitoring committee, its role and reporting structure {28a}

For this study, a separate Data Monitoring Committee has not been composed. Continuous monitoring of trial conduct and participant safety will be taken up by the Doctoral Committee supervising the doctoral thesis. The committee will review the progress of the study, discuss any concerns regarding data quality or participant safety, and advise the principal investigator.

### Frequency and plans for auditing trial conduct {29}

The Doctoral Committee shall convene a minimum of every six months to review the progress of trials, assess compliance with the approved protocol, and discuss operational or methodological problems identified during the study conduct. Issues noted during the review shall be documented and dealt with in a timely manner.

### Protocol amendments {31}

Any major protocol amendments, including changes to study design, eligibility criteria, interventions, outcomes, or analysis plans among others, will be submitted for approval to the Institutional Ethics Committee prior to implementation. Prior to this, proposed amendments will be reviewed and discussed during Doctoral Committee meetings. Relevant updates will also be communicated to the trial registry and documented in trial reports. They will also be communicated to the participants in case the revision(s) impact treatment and require the investigators to obtain an updated informed consent. Any deviations from the protocol will also be documented using a breach report form.

### Dissemination policy {8}

The results of the trial will be disseminated through publication in peer-reviewed scientific journals and presentation at relevant academic conferences.

## Discussion

This study will be the first attempt to examine the efficacy of Inhibitory Control Training (ICT) in reducing aggression among individuals with co-occurring substance use and gambling disorders in the Indian context. Drawing from the Problem Behavior Theory and the Dual Process Model of Addiction, the proposed intervention will target implicit mechanisms of behavior regulation by associating no-go cues with aggression-related stimuli. Unlike conventional therapies focusing on conscious reflection and decision-making, this paradigm makes use of unconscious processing to promote behavioral inhibition. As aggression is frequently observed in individuals with addictive behaviors and is closely linked to control and regulation, the intervention, if proven efficacious, could offer a cost-effective and time-efficient alternative to traditional cognitive-behavioral and anger management interventions. Conversely, should the intervention prove ineffective, the findings would indicate that this may not be a productive area for further exploration. Importantly, the study extends existing literature by contextualizing the intervention in India—a country where research on aggression and gambling in addiction populations remains underrepresented.

### Expected limitations and strengths

Among the strengths of the study is the use of a randomized controlled trial design that incorporates permuted block randomization and allocation concealment through the SNOSE method with well-structured active and placebo interventions. Another strength is the application of sham training on the control group which while controlling for time and attention, might also provide information into the underlying mechanism of functioning of this intervention. The use of multiple validated outcome measures ensures that all behavioural dimensions will be accurately recorded. Questionnaires are also being translated into Hindi, to maintain the consistency of questioning. Furthermore, assessments across four time points, including follow-ups at one-day post intervention, allow the investigation of both immediate and sustained effects. The individualized stimulus selection based on participant ratings may increase personal relevance, potentially increasing its effectiveness. Furthermore, the toolbox and the intervention prepared for this study can also be validated and applied on different populations, and for different treatment interventions.

However, along with the strengths, the limitations of the study must also be acknowledged. The study sample will be restricted to male inpatients with a specific diagnosis, which might limit its applicability to other populations. The same is the case with the development and validation of the study intervention. The intervention itself is brief, lasting only 3 days, and based on inconclusive mechanisms of work, which raises questions about its capacity in being capable of dealing with complex, chronic patterns of behavior. Lastly, the computerized nature of the task, although practical, may not be completely representative of real-world interactions of aggressive behavior.

### Expected outcomes

Despite these constraints, the research will inform us on the efficacy of this line of cognition-based interventional approaches in the Indian population. These kinds of interventions have not been tested in India before, and it might be useful to determine whether additional research along this line should be conducted. It is expected that individuals in the ICT group will exhibit significantly reduced overt aggression, as measured by the OAS-M, particularly at the one-month and three-month follow-ups. Improvements in inhibitory control are also anticipated. If proven efficacious, the underlying mechanism of the same may also be analyzed in terms of changes in the capacity for inhibitory control and ratings on the stimulus evaluation task. Given the interconnectedness of aggression, substance use, and gambling behavior, it will be assessed if reductions in aggression and improvements in inhibitory control may contribute to subsequent reductions in substance use frequency and gambling severity. Furthermore, participants in the ICT group may demonstrate generalization of the training effect to novel stimuli. This will be tested using ratings on other stimuli, and ratings on other stimuli not incorporated in the intervention.

In conclusion, this study has the potential to advance both theoretical understanding and clinical practice by introducing a resource-efficient intervention for a highly comorbid and underserved population. If successful, ICT may serve as an adjunct to conventional treatments, opening broader applications in addiction and behavioural health care.

### Trial status

The study protocol was developed as part of a three-to-five-year doctoral program starting from October 2023. The preparatory phase included constitution of a doctoral committee, development of the research protocol and subsequent modifications, followed by approval from the Institutional Ethics Committee and registration with the Clinical Trials Registry of India (CTRI). Participant enrolment was initiated on January 14, 2025, and is anticipated to complete in December 2026. Following this, analysis of the results and publication of the findings will be worked upon.

## Data Availability

The data can be made available upon completion and publication of the research study to researchers who provide a methodologically sound proposal to achieve the goals of the approved proposal. Any data required to support the protocol can also be supplied on request. Proposals should be submitted to the corresponding author.

